#### Primary statistical hypotheses

• Pain scores will be less, in those who received BTX-A, during the 5–10 days post-operative period compared to those who received saline injections (Specific aim 1).

• Pain scores will be less, in those who received BTX-A, at mid-distraction compared to those who received saline injections (Specific aim 1).

• The total amount of narcotic pain medication during the 10 days post-operative will be lower in those patients who received BTX-A than in those who received saline injections.

• Quality of life scores during mid-distraction will be higher in those who received BTX-A compared to those who received saline injections (Specific aim 2).

• Range of motion measurements and mobility scores will be improved in those who received BTX-A compared to those who received saline injections (Specific aim 3).

Primary Outcome Measures: FPS-r/NRS, PedsQL, ROM

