#### Inclusion Criteria

1. Age: 5 to 21 years.

2. Etiology of the deformity: congenital or acquired.

3. Amount of lengthening or deformity correction: any amount.

4. Site of lengthening or deformity correction: lower extremity, unilateral single segment.

5. Type of fixator: circular or uniplanar.

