### 2. Randomization

The randomization occurs at each site according to the procedure successfully used during the pilot. The bio-statistician consultant will generate a computerized block randomization schedule for each site ensuring an equal number of subjects in each group at each site. The coordinating site will provide each site with a set of sealed envelopes containing the randomization code for each patient, which will be opened only by the individual preparing the syringe. The patients will be randomly assigned to either the treatment group or the placebo group. Concealment of randomization will be enforced, so that individuals enrolling patients will be unaware of whether the next patient will be randomized to treatment or control [73,74].

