### 8. Pain Management Protocol

Pain management (assessment and treatment) guidelines are described in the study manual. Post operative pain medication is delivered via either PCA or epidural up to 72 h post-op. Pain assessment will be done using a 10 point scale (either Faces Pain Scale revised or the Numerical Rating Scale) according to post-operative PCA protocols; hourly for first 4 hours, every 2 hours for next 8 hours, and every 4 hours once stable. After the PCA/epidural is discontinued, PRN medications will be ordered for pain control, nausea/vomiting, itching, and fever during hospitalization. Pain assessments will also be done whenever a patient receives a PRN medication. All of this data will be recorded in the patient's chart along with the medication dosages administered.

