### 14. Statistical Analysis

Descriptive statistics will be calculated for all outcome variables and all relevant baseline variables. The data will be presented in summary tables, graphs, and listings to give an overview of the outcome and efficacy findings. The mean, median, standard deviation, and range of each variable and its change from baseline, measured on a continuous scale, will be presented by treatment and visit. Frequency tables will be provided for categorical variables by treatment and visit.

There are three primary outcomes: pain measured by the FPS-r or NRS, requirements of pain medication, and the quality of life using the PedsQL. The primary analysis for the pain will be performed during the post-operative (5–10 days) period as well as the mid-distraction phase. The primary analysis for the pediatric quality of life will be performed at mid-distraction and the mid-consolidation phase before the removal of the fixator. The primary analysis will be conducted using T-tests for continuous variables and chi-square and Fisher exact tests for categorical variables.

An interim analysis will be performed when 75 patients (1/2 the estimated sample size) have been enrolled, using the Obrien-Fleming group-sequential stopping rule. [82,83]

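### The 10-day narcotic total has no weight scaling, opioid conversion or covariate, and comparing it by an unadjusted t-test across ages 5 to 21 loses precision and leaves the unit unclear

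*Protocol article*

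**What the plan says.** Under 14. Statistical Analysis, the protocol article lists medication as primary: "There are three primary outcomes: pain measured by the FPS-r or NRS, requirements of pain medication, and the quality of life using the PedsQL". Under Primary statistical hypotheses, the matching hypothesis is: "The total amount of narcotic pain medication during the 10 days post-operative will be lower in those patients who received BTX-A". The Discussion again describes the measure as a total of narcotics. The test is fixed in section 14: "The primary analysis will be conducted using T-tests for continuous variables and chi-square and Fisher exact tests for categorical variables".

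The setting comes from other sections. Inclusion Criteria: "Age: 5 to 21 years". Section 8, Pain Management Protocol: "Post operative pain medication is delivered via either PCA or epidural up to 72 h post-op", followed by PRN medication. Section 2 has the statistician "generate a computerized block randomization schedule for each site ensuring an equal number of subjects in each group at each site". The stratification section uses indication and severity. Age appears only among the further analyses under Secondary Analysis. Weight and analgesic route are not named as stratification factors or covariates anywhere in the article.

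The article is not consistent on the status of this outcome. The list that closes Primary statistical hypotheses reads "Primary Outcome Measures: FPS-r/NRS, PedsQL, ROM" and leaves medication out.

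**The concern.** Eligible ages run from early childhood to adulthood, so body weight will differ several-fold between patients. Two patients with the same opioid use per kilogram can have very different totals. The protocol scales its own study drug by weight but states no such scaling for the narcotic outcome. An unadjusted t-test on the total puts all the weight variation into the error term, where it dilutes any treatment difference.

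There is also a question of meaning. PCA, epidural and later PRN opioids can differ in agent and route. Without a conversion, their doses do not add up to one quantity, whatever the variances are. At stake are the power and the readability of an outcome that section 14 names as one of three primary outcomes.

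**Working it through.** **1. The plan's own figure.** The Sample size section states 75 per group, effect size 0.45, alpha 0.05 and 80% power. For a two-sided test, power ≈ Φ(d·√(n/2) − 1.96). With d = 0.45 and n = 75, this is Φ(0.45 × 6.124 − 1.96) = Φ(0.796) = 78.7% (exact t: 78.2%). The stated 80% is reproduced to within two points. The effect size is justified on the PedsQL, and no SD for narcotic use is given.

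**2. Assumptions.** The article gives no distribution of weight or opioid use. I assume that per-kg use has CV 50%, that weight has CV 40%, that the two are independent, and that the true reduction is 25%.

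**3. Variance of the unscaled total.** The total is per-kg use times weight, so

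CV²(total) = CV²(dose) + CV²(weight) + CV²(dose)·CV²(weight) = 0.25 + 0.16 + 0.04 = 0.45, and CV(total) = 0.671.

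**4. Effect on power at 75 per arm (exact t).**
- Per-kg scale: d = 0.25/0.50 = 0.50, power 86.0%.
- Unscaled total: d = 0.25/0.671 = 0.373, power 62.1%.
- Sample-size ratio: 0.45/0.25 = 1.80.

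**5. Range of CVs.**
- Dose CV 60%, weight CV 30%: 0.4824/0.36 = 1.34.
- Dose CV 40%, weight CV 50%: 0.45/0.16 = 2.81.

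The sample-size penalty therefore runs from about 1.3 to 2.8. Starting instead from the plan's d = 0.45 on the per-kg scale, with dose CV 40 to 80% and weight CV 25 to 45%, power on the unscaled total is 42 to 73%.

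**6. If independence fails.** Let both quantities be lognormal with log-scale correlation ρ. The log variances are ln 1.25 = 0.223 and ln 1.16 = 0.148, and the product of the log SDs is 0.182. The log variance of the total is 0.223 + 0.148 + 2ρ × 0.182. At ρ = −0.3 it is 0.262, so CV² = e^0.262 − 1 = 0.300. The sample-size ratio is then 0.300/0.25 = 1.20, d = 0.25/√0.300 = 0.456 and power is 79%. The penalty disappears near ρ = −√0.148/(2√0.223) = −0.41.

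**7. Validity.** In simulations with no treatment effect, with and without a route difference, the type I error of the t-test on the total stayed at 4 to 5%.

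**8. Route and agent.** Any figure here would depend entirely on an assumed share of epidural patients and an assumed ratio of the dose scales. The article gives neither, so none is claimed.

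**The case against.** The strongest objection is that the hypothesis is one sentence in a journal article. It fixes accumulation over 10 days but not the unit, so a per-kg or morphine-equivalent total would also fit it. Pain guidelines sit in a study manual that is not shown. This stands in part: an unscaled total is the plain reading, not an explicit statement. But the article does fix the quantity as a total and the test as an unadjusted t-test. If another definition exists, the published wording should be replaced by it.

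Second, the size rests on assumed CVs, independence and an assumed 25% effect. That is correct, and step 6 shows that the penalty can largely vanish if per-kg use falls with weight.

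Third, a reader might infer that weight and route swamp the treatment signal. The documents do not support this: they give no variance for either, and 62% power is dilution.

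Fourth, a reader might infer that chance imbalance in weight or route biases the comparison or inflates false positives. It does not. Assignment is randomized, concealed and blinded, and the test's error rate already allows for chance imbalance.

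Finally, PCA or epidural covers at most 72 hours of the 10 days, and the article does not say which drugs the epidural contains. That limits what can be said about the size of the route effect. It does not remove the need for a common unit.

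**Conclusion.** The point holds as a loss of precision and an unclear unit. Followed as written, the comparison would have about 62% power where a per-kg analysis would have about 86%, given a dose CV of 50%, a weight CV of 40%, independence and a 25% reduction. None of these inputs comes from the documents. Across the CV range tried, the sample-size penalty is 1.3 to 2.8 under independence, and it is smaller if per-kg use declines with weight. The lack of a common unit across agents and routes needs no variance assumption, but its effect on power cannot be quantified here. The t-test remains valid, so no bias is alleged. The primary status of the outcome is itself contradictory within the article.

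**What to change.** - **Outcome.** Define it as cumulative morphine-equivalent dose per kg body weight over the 10 post-operative days, using one prespecified conversion table that covers epidural and PRN opioids.
- **Analysis.** Replace the unadjusted t-test with a model adjusting for age, site and the analgesic route planned before the injection. Use the planned route so that the covariate cannot be affected by treatment. Use the log scale or ranks if the data are skewed; ranks also cope with zero totals.
- **Timing.** Set this before the interim analysis at 75 patients, because section 10 allows that analysis to stop the trial.
- **Status.** Reconcile the section 14 statement that medication is primary with the closing list of primary measures that omits it.

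The cost is small but not nil. Weight is already needed to dose the injection, and inpatient dosages are already extracted. Agent and route are not named among the items recorded on the chart form or in the family journal, so their capture must be confirmed. The journal matters because the planned stay is 4 to 7 days, so the later days of the 10-day total are recorded by the family. Otherwise the work is a conversion table and a few lines of analysis text.

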#### Secondary Analysis

Secondary longitudinal analyses will be carried out and include several time periods and compare additional variables as shown in the following table. Stratification by age or site of fixator or type of surgery (lengthening versus correction) will allow further analyses. T-tests and analyses by repeated measures will be used for the secondary analyses.

#### Sample size

The proposed sample size of 75 per group provides 80% power to detect an effect size of 0.45, with alpha = 0.05. The effect size of 0.45 corresponds to a difference of approximately 7.5 in the PedsQL (Ref Varni et al 2002, Varni et al 2003). This difference is smaller than that found in studies comparing children with chronic diseases to healthy children. The following table provides a range of options for sample size, using the PedsQL as an example. For a standard deviation (SD) of 15 and alpha (type I error) of 0.05, the power is as given in the first column for different values of delta (the detectable difference between the groups). The differences detected in the pilot work support the planned sample size.

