### 1. Sample and Duration of Study

Subjects will be recruited at each site from patients requiring surgery for limb lengthening or deformity correction using distraction with a fixator. The 6 sites participating in the study include Shriners Hospital for Children in Montreal, Honolulu, Philadelphia and Portland as well as DuPont Hospital for Children in Wilmington, Delaware and Hospital for Sick Children in Toronto, Ont. Based on the historical data at each site for 2003–2006, estimations were made of potential participants for each site. The mean number of children treated for this problem at each participating site varies from 8 to 30 for a total of approximately 75 potential participants per year for the 6 sites.

The total sample size expected to meet the inclusion criteria is approximately 150 subjects to be recruited over 2 years (See section 10 for a detailed power calculation). Subjects will be randomized to either an injection of BTX-A (BTX-A group) or normal saline (control group) and both will continue with standard post-operative nursing care and rehabilitation. Patients undergoing this particular intervention are closely followed in the outpatient clinic after discharge. At each visit they routinely meet the surgeon, the Care Coordinator, and the physical therapist. The site coordinator will track the participants and ensure that the standardized assessments are administered at the appropriate visit.

Subjects will be enrolled during the first 24 months of the 3-year project. Each patient is followed for up to 12 months with data collected longitudinally over this period. The last patients enrolled in year 2 will be followed for 9–12 months into year 3. No recruitment will occur in year 3, however, follow-up on the final patients enrolled in year 2 will continue into the final months of year 3. Analysis will commence in year 3. Depending on the timing and number of participants enrolled in year 2 a continuation to year 4 may be required for final statistical analysis.

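### At the only SD stated (15), an effect size of 0.45 is 6.75 PedsQL points, not 7.5, and whether 75 per group leaves any reserve depends on which figure is meant

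*Protocol article*

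**What the plan says.** All the sizing figures are in the protocol article, section 14, under Sample size.

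- Size and power: "The proposed sample size of 75 per group provides 80% power to detect an effect size of 0.45, with alpha = 0.05".
- Translation to the quality-of-life scale, for which two PedsQL publications are cited: "The effect size of 0.45 corresponds to a difference of approximately 7.5 in the PedsQL".
- Shortly afterwards, to introduce a table of sample-size options with the PedsQL as the example: "For a standard deviation (SD) of 15 and alpha (type I error) of 0.05". No other SD appears in the article.
- Test, from the opening of section 14: "The primary analysis will be conducted using T-tests for continuous variables".

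Section 1 (Sample and Duration of Study) gives the supply of patients, from historical counts at the sites: "for a total of approximately 75 potential participants per year for the 6 sites". It expects about 150 eligible subjects over two years and rules out recruitment in year 3. The possible extension to year 4 is for final analysis.

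**The concern.** An effect size is the difference divided by the SD, so any two of the three figures fix the third. Here 0.45, 7.5 and 15 are given for the same instrument within one paragraph, and they do not fit together. A reader cannot tell whether the trial is sized for 6.75 points, for 7.5 points at SD 15, or for 7.5 points at some larger SD that is not shown.

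This affects how a null PedsQL result would be read, because the difference the trial could reliably detect is unclear. It also decides whether the planned number contains any reserve. That matters because the planned number equals the whole expected pool, and recruitment is not planned to continue into year 3.

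**Working it through.** **Inputs.** From Sample size: 75 per group, 80% power, effect size d = 0.45, difference 7.5, SD 15, alpha 0.05. From section 14: t-test. From section 2 (Randomization): equal groups. From section 1: about 75 potential participants a year for two years. The article does not state whether alpha is one- or two-sided, so both were tried.

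**1. The stated power.** Normal approximation, two-sided: power = Φ(d × √(n/2) − 1.96).
- d × √(n/2) = 0.45 × √37.5 = 2.756, and Φ(2.756 − 1.96) = 78.7%.
- The exact t-test gives 78.2%.
- One-sided, the result is 86.7%, which does not match. The two-sided reading is therefore used below.
- The effect detectable with 80% power at 75 per group is 2.80 × √(2/75) = 0.457 (t-test 0.460).

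So the statement "provides 80% power to detect an effect size of 0.45" is reproduced to within rounding.

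**2. The conversion.** Difference = d × SD.
- 0.45 × 15 = 6.75 points.
- 7.5 / 15 = 0.50.
- 7.5 / 0.45 = 16.7, the SD needed for the stated pair.
- Allowing for rounding of both figures, the SD lies between 7.25/0.455 = 15.9 and 7.75/0.445 = 17.4. The value 15 is outside this range, so the word for approximation in the sentence does not close the gap.

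**3. What each reading implies.** Per-group size for 80% power = 2 × (1.96 + 0.84)² / d², then the t-test value.

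| Reading | Effect size | Needed per group for 80% (normal / t) | Power at 75 per group (t) |
|---|---|---|---|
| 6.75 points, SD 15 | 0.45 | 78 / 79 | 78.2% |
| 7.5 points, SD 15 | 0.50 | 63 / 64 | 86.0% |
| 7.5 points, SD about 16.7 | 0.45 | 78 / 79 | 78.2% |

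**4. Reserve.** Pool: 2 × 75 = 150. Planned: 2 × 75 per group = 150. The two are equal. The article gives no rates of refusal or loss, so the combined shortfalls below are assumptions (t-test power).

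| Assumed shortfall | Evaluable per group | Power at 0.45 | Power at 0.50 |
|---|---|---|---|
| 0% | 75 | 78.2% | 86.0% |
| 10% | 67.5 | 73.7% | 82.2% |
| 15% | 63.75 | 71.3% | 80.0% |
| 20% | 60 | 68.6% | 77.5% |
| 30% | 52.5 | 62.7% | 71.8% |

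At 0.50 the reserve is 1 − 64/75 = 14.7%, about 15%. At 0.45 there is none.

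**The case against.** The strongest defence is that the article never says 0.45 equals 7.5 points at SD 15. It cites publications for that correspondence and brings in SD 15 afterwards, for an illustrative table. An SD near 16.7 may lie behind the pair. This stands as a possible explanation, and for that reason it is one of the three acceptable resolutions below. It does not remove the point: the SD behind the conversion is not stated, and the one printed for the same scale in the same paragraph does not reproduce it. The options table is not available here, and nothing above depends on it.

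Three stronger readings are tempting, and the document does not support them.

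- A reader might infer that the 80% is itself wrong, because 79 rather than 75 per group are needed at 0.45. The gap is 78.2% against 80%, or a detectable effect of 0.46 against 0.45. That is rounding.
- A reader might infer that 80% power requires every eligible child to enrol and none to be lost. At 0.50 this is false, since 64 per group suffice. At 0.45 it does not fit exactly either, since full enrolment with no loss gives 78%.
- A reader might treat the absence of a loss allowance as an omission. A journal article may leave that to the full protocol. The point here rests only on figures the article does state: the planned size, the pool and the end of recruitment.

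The timing of the quality-of-life endpoint should not be overstated. Section 14 places it at mid-distraction and mid-consolidation, and its hypothesis names mid-distraction. On the Background's figures (5 to 7 days of latency, 1 mm a day), mid-distraction of a 5 cm lengthening falls 5 to 7 days plus 25 days after surgery, about a month. Only mid-consolidation is months away.

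**Conclusion.** The point holds as an inconsistency in the conversion, not in the stated power. The figures 0.45, 7.5 and 15 cannot all be right. The mismatch is 0.75 points on the PedsQL, or 0.05 in effect size, and it moves the number needed for 80% power from 79 to 64 per group.

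Neither reading overturns the planned 75 per group if all are evaluable: power is 78% or 86%. The practical difference is the reserve. If 0.45 is the target, any refusal or loss takes power further below the stated 80%, and the pool as estimated cannot replace those children. If 0.50 is the target, a combined shortfall of about 15% is covered.

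This rests on a two-sided, two-sample t-test at 0.05 with equal groups. The pool is an approximate historical estimate, and the shortfall rates are illustrative.

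**What to change.** State one matching set of difference, SD and effect size. Three are coherent, and the choice is the sponsor's:

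- 6.75 points, SD 15, effect size 0.45: 78% power with 75 evaluable per group.
- 7.5 points, SD 15, effect size 0.50: 86% power with 75 evaluable per group, and 80% with 64.
- 7.5 points, SD about 16.7, effect size 0.45: 78% power with 75 evaluable per group, with the source of the SD given.

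Then restate the power that 75 per group gives for the chosen set, say that the test is two-sided if that is intended, and add a line with the power if fewer than 75 per group are evaluable. That line should note that the planned 150 equals the estimated two-year pool.

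The cost is a rewording of the sample-size paragraph. No patients are added. If 0.45 is kept, the stated power becomes slightly less favourable.

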## Discussion

The global aim of this proposal is to determine if BTX-A can alleviate the post-operative pain and improve the functional outcome of children undergoing limb lengthening or deformity correction.

We have decided to measure in the post op period both the total amount of pain as well as the total amount of narcotics since both parameters are interconnected. Some patients may have very little pain but on the other hand may have received large doses of narcotics, therefore it is important to measure and record both parameters.

The mobility variables, weight bearing, range of motion and level of ambulation are indicative of a higher level of participation. In addition, an increased level of mobility is associated with lengthenings that have fewer complications such as delayed healing.

Reduced pain and increased mobility are felt to contribute to an improved quality of life for children undergoing lengthening. Clearly, these key variables are linked during the long and painful process of distraction osteogenesis and botox may assist in initiating this process.

